### Randomization and client recruitment

A stratified blocked randomization procedure will assign facilities to intervention arms. Each of the three strata consisting of eight ‘equivalent’ supportive living facilities will be randomized separately to four intervention arms by first constructing two blocks of four facilities within each stratum. Using computer-generated random numbers, facilities within each block will be randomized to one of the four intervention arms. Block randomization ensures that an equal number of ‘equivalent’ facilities are assigned to each of the four arms. Research assistants will recruit clients to participate throughout the study with replacement when a client moves or dies. Clients will be eligible to participate if they can transfer independently or with the assistance of one person.

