#### Sample size calculation for primary outcome

The required sample size for the trial is 24 facilities, each with an average of 15 health care aides assigned to two clients. Each aide is expected to have 1,440 (2 × 2 × 30 × 12) possible uptake occasions with each client, for an expected total of 43,200 (15 × 2 × 1,440) aide-occasions per facility over the trial’s duration. The sample size calculation, based upon previous results from four facilities consisting of 44 aides [7,50], yielded an estimated non-interventional uptake rate of 22.6% with a coefficient of variation (CV) of 0.54 among facilities. The CV plays the role of the between-facility clustering parameter in the sample size formula for rates [51]. For the purpose of sample size calculations, we assume the low-low arm to have an uptake rate of 20%, the single-high arms to have an uptake rate of 55%, and the double-high arm to have an uptake rate of 90%. The additive trial design has 80% power at a 5% two-sided level of significance to detect a 93.3% relative increase in the marginal rates of uptake (72.5% versus 37.5%) between high and low (Figure 3).

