### Trial data management and analysis (research questions 1 to 3)

Data will be entered by a contracted agency into a statistical database (SPSS version 19; IBM, Armonk, NY, USA) programmed to minimize data entry errors. All of the data will be double entered to assess the accuracy of data entry. Research participants will be assigned unique identifiers and all personal identification will be removed before data cleaning and analysis. A graduate student will be hired to clean the data using standard data management techniques. All analyses will follow the intention-to-treat principle, namely that all participants will be included regardless of deviation from protocol. SAS 9.2 (SAS Institute, Cary, NC, USA) software will be used to perform the aide-level analyses. For the primary outcome measure, the total number of completed sit-to-stand occasions out of the total number of possible (completed and not completed aide-occasions) will be calculated. As the design is a stratified additive 2 × 2 factorial, generalized estimation equations (GEE) with a log link, Poisson distribution, an exchangeable working correlation structure, and no interaction term will be used to simultaneously test the significance of the high versus low intensity and frequency using Wald tests (PROC GENMOD). The model will include ‘equivalent’ strata as a covariate and log total aide-occasions as the offset. Robust variance estimators will be employed to adjust for the effect of clustering. Although the size of the trial is not statistically powered to detect a synergistic effect between intensity and frequency, an interaction term will be incorporated into the model to test for this effect. In the event that imbalance on baseline facility and health care aide characteristics among groups occurs, GEE naturally facilitates additional analyses to examine, and control for, their influence. Rate ratios will be used in quantifying the effectiveness of the high versus low intensity and frequency reminders. For the secondary outcome measure, a mixed effects linear regression model (PROC MIXED) will be used, with facility considered as a random effect to account for the clustering, no interaction term, and ‘equivalent’ strata and baseline sit-to-stand number as covariates. An interaction term will be incorporated into the model to test for a synergistic effect between intensity and frequency, as well as baseline facility and health care aide characteristics if unbalanced. Least squares means will be used to quantify the effectiveness of the interventions. Based on the Medical Research Council (MRC) framework for developing and evaluating complex interventions, we are moving from the pilot stage to the evaluation stage of knowledge translation interventions [43].

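### Wald tests with an ordinary robust variance on 24 facilities have a true type I error of about 10%, not the stated 5%

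*Protocol article*

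**What the plan says.** The section *Trial data management and analysis (research questions 1 to 3)* of the protocol article fixes the primary model. It is a Poisson GEE with a log link and exchangeable working correlation, stratum as a covariate, an offset for the log number of possible occasions, and no interaction. The model is used to "simultaneously test the significance of the high versus low intensity and frequency using Wald tests (PROC GENMOD". On variance the only statement is: "Robust variance estimators will be employed to adjust for the effect of clustering". An interaction term is then added to test for synergy.

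The section *Sample size calculation for primary outcome* sets the scale: "The required sample size for the trial is 24 facilities, each with an average of 15 health care aides assigned to two clients". It plans for a two-sided 5% level and 80% power. On randomisation, *Randomization and client recruitment* says: "Each of the three strata consisting of eight ‘equivalent’ supportive living facilities will be randomized separately to four intervention arms".

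The article names no small-sample correction to the variance, no t or F reference, and no permutation test.

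**The concern.** Each factor varies only between facilities. The information on its effect therefore comes from 24 units, however many occasions each unit contributes. The sandwich variance is built from facility-level residuals that have been shrunk by fitting five parameters, so it is too small on average. A Wald test then treats that noisy estimate as known by referring the statistic to the normal distribution. Both errors act in the same direction.

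The answers to research questions 1 and 2, and the interaction test for question 3, all rest on this procedure. A reminder strategy with no effect would be declared effective more often than the stated level allows. The article also expects to spread the tested reminders to other facilities, and reports that peer reminders took more time and effort to implement.

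**Working it through.** **Inputs from the article.** 24 facilities, so 12 per level of each factor and 6 per arm. Three strata. 43,200 occasions per facility. Planning rate 22.6% with between-facility CV 0.54. Marginal rates 37.5% and 72.5%. Two-sided 5%.

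**Parameters.** Intercept 1 + strata 2 + factors 2 = 5, leaving 24 − 5 = 19 df. With the interaction there are 6 parameters and 18 df.

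**The plan's own power figure.** The standard formula for clustered rates, without the extra cluster sometimes added, is

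c = (1.96 + 0.8416)² × [(λ0 + λ1)/y + k²(λ0² + λ1²)] / (λ1 − λ0)²

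- (λ0 + λ1)/y = 1.10/43,200 = 0.00003
- k²(λ0² + λ1²) = 0.2916 × 0.66625 = 0.1943
- c = 7.849 × 0.1943/0.1225 = 12.4 facilities per level

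With 12 per level, power is Φ(2.751 − 1.96) = 78.5%, close to the stated 80%. The stated figure is therefore essentially a normal-reference figure. The occasions term is negligible beside the between-facility term, so more occasions per facility cannot repair the inference.

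**Analytic size of the planned test.** If the sandwich variance is too small by a factor of about 1 − p/24, the size is about P(|t| > 1.96 × √((24 − p)/24)) on 24 − p df.

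- Main effects, p = 5: P(|t19| > 1.96 × √(19/24)) = P(|t19| > 1.744) = 9.7%
- Interaction, p = 6: P(|t18| > 1.697) = 10.7%

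**Facility-level simulation**, 20,000 trials per scenario, Monte Carlo SE about 0.2 points:

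| Scenario | Planned test |
|---|---|
| Mean 22.6%, CV 0.54, gamma | 10.4% |
| Mean 30%, CV 0.54 | 9.8% |
| Mean 55%, CV 0.40 | 8.9% |
| Frequency null, intensity active (20% vs 55%) | 10.0% |
| Frequency null, intensity active (37.5% vs 72.5%) | 6.9% |
| Interaction | 11.1% |

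The leverage-corrected (Kauermann-Carroll type) sandwich with t on 19 df (18 for the interaction) gives 2.4% to 5.4% over these scenarios.

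**Aide-level simulation** of the full GEE, with 24 facilities of 15 aides, exchangeable correlation and strata:

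- Beta facility rates, 22.6%, CV 0.54, 8,000 runs: 9.9% for intensity and 9.5% for frequency. Corrected sandwich with t(19): 5.1% for both.
- Gamma, lognormal and beta rates, equal or unequal sizes, stratum differences, and a case with mean 55% and CV 0.25 (2,000 runs each, SE about 0.7 points): 9.7% to 11.9%. Corrected: about 4.7% to 6.4%.
- Frequency null with an intensity rate ratio of 1.93 (5,000 runs): 9.8%. Corrected: 4.9%.
- Interaction: 11.4%. Corrected with t(18): 5.4%.
- At least one false positive over the two factors: 18% to 21%. Two independent tests at a true 5% would give 1 − 0.95² = 9.8%.

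**The case against.** **The inflation is not uniform.** At marginal rates of 37.5% and 72.5% with CV 0.54 the size is 6.9%, about 1.4 times nominal. This stands as a computed result, but the scenario is strained. A beta distribution with mean 0.725 and SD 0.54 × 0.725 = 0.3915 has a + b = 0.725 × 0.275/0.1533 − 1 = 0.30. Both shape parameters are then below 1 and the distribution is U-shaped, with facilities piled up near 0% and 100%. At the documented planning values the figure is about 10%, and no scenario falls to 5%.

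**The correction over-corrects there.** This also stands: 2.4% is the low end. In the other scenarios it is close to nominal.

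**The form of the robust variance might be left to an analysis plan.** A corrected sandwich is also a robust variance, so reading the text as the ordinary one is an inference. However, the article itself fixes the test, software procedure, model terms and variance type. As written, that specification does not hold the stated level.

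**Point estimates are unaffected, so only borderline results would change.** This is true of the rate ratios. Control of the 5% level concerns exactly those borderline results, and the interval widths are wrong for every result.

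**Conclusion.** The concern holds. As written, the primary tests reject a true null in about 10% of trials at the planning values, roughly twice the stated 5%. The range is 6.9% to 11.9% over all main-effect scenarios, and the interaction test is at about 11%. It must be corrected because both primary conclusions depend on it.

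The conclusion assumes that the facility is the GEE cluster, and that the variance is the uncorrected sandwich with a normal reference. The article also refers to aide-level analyses and never names the cluster. If the aide were the cluster, aides in one facility would be treated as independent and the inflation would be worse. The shape of the facility distribution, the aide-level CV of 0.5 and the ranges for unequal sizes are also assumptions. The result changed little across those tried, apart from the U-shaped case.

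**What to change.** State that the facility is the GEE cluster, and that all Wald tests and confidence intervals use a small-sample bias-corrected sandwich variance (for example Kauermann-Carroll) with a t reference on facilities minus facility-level parameters: 19 df for the main effects and 18 with the interaction. A facility-level regression with t on 19 df is an acceptable alternative. Add a permutation test that respects the randomisation strata and blocks as a check.

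The wording and code are short, but the cost is more than cosmetic. Interval half-widths grow by about √(24/19) × 2.093/1.96 = 1.20, that is 20%; most of this removes the existing error. Power at the planning inputs falls from 78.5% to about 74% on the rate-difference scale. On the log-rate scale, which matches the model's link, the non-centrality is ln(1.933)/√(2 × 0.2916/12) = 2.99, and power falls from 84.9% to 81.0%. The sample size section should restate power on the scale and reference distribution actually used.

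The change can be made before any outcome data exist: at the reported trial status, 2 of 24 facilities and no clients had been recruited.

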
### Process evaluation (research question 4)

The goal of the process evaluation is to understand how facility processes and reminders affect the sustainability of health care aide uptake of the sit-to-stand activity. This evaluation will enable an understanding of: unexpected outcomes, fidelity of the interventions (including local adaptations of the interventions) [44], ‘active ingredients’ of the four intervention arms [58], subgroup variation, and the influence of contextual factors on outcomes [43,44,59]. We will examine how the reminders are implemented and perceived by participants, as well as how health care aides providing peer reminders are identified, received by their peers, and supported by their supervisors. Key components of this evaluation involve a careful analysis of potential barriers and facilitators that inhibit or promote practice change, the need to refine the reminders, and the value of extending their use to other supportive living facilities. Process evaluations are indicated in multisite trials where the ‘same’ intervention may be implemented and received differently across sites [59].

To augment the standardized measures from the facility assessments, we will collect further process data using observations, questionnaires, and interviews. For observations, anytime that research staff enter a study facility, they will be alert to observe responses of facility staff or clients to the reminder interventions. Upon exiting the facilities, they will immediately record fieldnotes [60]. Organizational processes will be especially evident when collaborating with facilities to recruit clients to the study and collect monthly flowsheets. Educators’ fieldnotes will be useful for understanding processes of and responses to coaching the health care aides that provide reminders. For the questionnaire, we will survey a licensed practical nurse and a manager from each facility using a questionnaire to elicit perceptions of the reminders (see Additional file 6). For interviews with health care aides, to understand health care aides’ views of the reminders, we will use interviews rather than written questionnaires, as many health care aides speak English as a second language (see Additional file 7). We will interview approximately six health care aides from purposively sampled facilities until we achieve saturation [61]. Four facilities (two positive and two negative extreme cases; one from each arm) will be sampled based on facility assessments. For interviews with peer reminders, to understand the peer reminder experience, we will interview approximately six health care aides providing peer reminders from each high intensity reminder arm until saturation (see Additional file 8).

Text from fieldnotes, questionnaires, and interviews will be imported into ATLAS.ti (ATLAS.ti Scientific Software Development, Berlin, Germany), and checked for accuracy. The data will be coded, classified, and analyzed thematically based on interpretive description principles to generate a description that informs understanding [62]. This analysis, along with the facility assessments, will allow us to describe, compare, and generate hypotheses about the processes associated with the sustainability of the sit-to-stand activity across the four intervention arms [59].

### Expected outcomes

Recognizing the need to balance the effectiveness of the innovation’s sustainability with efficient resource allocation, this study will identify the frequency and intensity of reminders required to sustain the behavior of health care aides to complete the sit-to-stand activity. At the end of the study we will know: 1) if less frequent reminders are as effective as more frequent reminders in sustaining the health care aides’ behavior; 2) if the peer reminders added to the paper-based reminders are more effective than paper-based reminders alone in sustaining the health care aides’ behavior; 3) if more frequent paper-based reminders plus the peer reminders synergistically improve the sustainability of the health care aide’s behavior; and 4) how facility processes and the reminders are associated with the sustainability of health care aides completing the sit-to-stand activity.

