### Research questions

1. Do more frequent reminders (every month) improve the sustainability of the sit-to-stand activity by health care aides in supportive living facilities compared with less frequent reminders (every 3 months)?

2. Do high intensity reminders (paper-based reminders plus peer reminders) improve the sustainability of the sit-to-stand activity by health care aides in supportive living facilities compared with low intensity reminders (paper-based reminders only)?

3. Do more frequent reminders plus high intensity reminders synergistically improve the sustainability of the sit-to-stand activity by health care aides in supportive living facilities?

4. What are the processes associated with the ongoing uptake of the sit-to-stand activity over a year of follow-up?

### Hypotheses for research questions 1 to 3

1. Arm 1 with low intensity and low frequency reminders will have poor uptake of the activity.

2. Arm 2 with low intensity and high frequency reminders will have moderate uptake of the activity.

3. Arm 3 with high intensity and low frequency reminders will have moderate uptake of the activity.

4. Arm 4 with high intensity and high frequency reminders will have excellent uptake of the activity.

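### Expected outcomes promises to show whether less frequent reminders are as effective, but hypothesis, sample size and test address only superiority, so the trial cannot establish that

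*Protocol article*

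**What the plan says.** The Expected outcomes section of the protocol article lists what will be known when the study ends. Item 1 is "if less frequent reminders are as effective as more frequent reminders in sustaining" the aides' behaviour. The sentence that opens the section gives the motive: sustained effect has to be balanced against the resources it takes. Item 3 says it will also be known whether frequency and intensity act synergistically.

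Elsewhere the frequency comparison is framed as superiority:

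- **Research questions**, question 1: "Do more frequent reminders (every month) improve the sustainability of the sit-to-stand activity by health care aides in supportive living facilities", with reminders every 3 months as the comparator.
- **Sample size calculation for primary outcome**: 24 facilities give 80% power at a two-sided 5% level "to detect a 93.3% relative increase in the marginal rates of uptake", that is, 72.5% versus 37.5%.
- **Trial data management and analysis**: a Poisson GEE without interaction will "simultaneously test the significance of the high versus low intensity and frequency using Wald tests (PROC GENMOD"). The effect measure follows: "Rate ratios will be used in quantifying the effectiveness of the high versus low intensity and frequency reminders".

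On synergy, the same analysis section says: "Although the size of the trial is not statistically powered to detect a synergistic effect between intensity and frequency", an interaction term will be added to test for it.

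**The concern.** A claim that one schedule is as effective as another needs evidence that any loss is small enough to accept. A test of no difference does not supply it. If it rejects in favour of monthly reminders, the less frequent schedule is shown to be worse. If it does not reject, the question stays open unless the confidence interval is narrow.

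The wording bears on the decision the trial is meant to inform. Item 2 of the same list uses superiority language for intensity. Only the frequency item is turned round into equal effectiveness, and equal effectiveness is what would justify the cheaper quarterly schedule. With the trial sized for a near doubling of uptake, a non-significant frequency effect is quite possible when monthly reminders are better by an amount a facility would care about. A reader holding item 1 could then take that result as support for quarterly reminders.

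Item 3 has a smaller problem of the same kind: it promises an answer on synergy that the analysis section says the trial is not powered to give.

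**Working it through.** **Inputs.** From the sample size section: 24 facilities, between-facility CV k = 0.54, marginal rates 0.375 and 0.725, 43,200 aide-occasions per facility, two-sided 5%, 80% power. Randomization is equal across four arms, so each factor compares 12 with 12 facilities. The effect measure is the rate ratio (RR), here monthly over every 3 months. Two inputs are assumptions: 19 degrees of freedom for the t reference (24 facilities less one intercept, two stratum terms and two factor terms), and a CV of 0.30 as an optimistic alternative.

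**Step 1. Reproduce the plan's power.** The cluster-trial formula for rates, without the correction of one extra cluster per level, is

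c = (1.96 + 0.842)² × [(λ0 + λ1)/y + k²(λ0² + λ1²)] / (λ1 − λ0)²

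- Within-facility term: 1.10/43,200 = 0.000025, which is negligible.
- Between-facility term: 0.2916 × (0.1406 + 0.5256) = 0.1943.
- Divided by 0.35² = 0.1225, this gives 1.586.
- c = 7.849 × 1.586 = 12.45 facilities per level, about 25 in total against 24 stated.
- Power with 12 per level: Φ(√(12/1.586) − 1.96) = 78.5%.

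This is close to the stated 80%, so the inputs are read as the plan intends.

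**Step 2. Precision on the planned effect measure.** With within-facility error negligible,

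SE(log RR) = √(2k²/12) = √(2 × 0.2916/12) = 0.2205.

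As a check, this scale with t on 19 df gives 81% power at RR 1.933, in line with the plan.

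For an observed RR of exactly 1.0, the 95% interval is exp(±2.093 × SE):

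| CV | SE(log RR) | 95% interval around 1.0 |
|---|---|---|
| 0.54 (plan) | 0.2205 | 0.63 to 1.59 |
| 0.30 (assumed) | 0.1225 | 0.77 to 1.29 |

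With 1.96 in place of 2.093, the intervals are 0.65 to 1.54 and 0.79 to 1.27. On the plan's CV, even a perfect tie could not rule out a relative advantage of over 50% for monthly reminders.

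**Step 3. How often a real benefit would be non-significant.** Noncentral t, 19 df, noncentrality log(RR)/SE:

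| True RR | Power, CV 0.54 | Non-significant, CV 0.54 | Non-significant, CV 0.30 |
|---|---|---|---|
| 1.25 | 16% | 84% | 59% |
| 1.50 | 42% | 58% | 12% |
| 1.75 | 67% | 33% | 1% |

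The absolute-scale formula of step 1, with 37.5% as the lower rate, gives nearly the same power at CV 0.54: 17%, 43% and 67%.

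**Step 4. Would adding a margin rescue the claim?** The article gives no margin, so these are assumed. With true equality, one-sided 2.5% and CV 0.54, power to show that quarterly reminders are non-inferior is Φ(−log(m)/0.2205 − 1.96), where m is the margin for the ratio of quarterly to monthly uptake. For m = 0.90, 0.80, 0.75 and 0.67 this is 7%, 17%, 26% and 44%. None reaches 50%.

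**The case against.** The strongest reply is that the operative plan is consistent. The research question, the arm-by-arm hypotheses, the sample size and the analysis all concern superiority, and the superiority test is sound. Expected outcomes is a narrative list that follows the research questions in order, and item 1 can be read as a loose converse of question 1. It says the study will show *if* the schedules are equally effective, and a significant test would validly answer no. This stands, and it makes the point one of wording rather than of design. It does not rescue the affirmative answer, which no stated analysis can deliver.

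A reader might go further and infer that the investigators intend to treat a non-significant result as equivalence. The article does not say so anywhere, and rate ratios reported with intervals would reveal the imprecision.

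The figures also depend on the CV. The value of 0.54 comes from four facilities at 22.6% uptake. Applied at 72.5% it implies a between-facility SD of 0.54 × 0.725 = 0.39, so one SD above the mean exceeds 100%. A constant CV is therefore doubtful at high uptake, and the calculation gives no credit for stratification. At CV 0.30 a true ratio of 1.5 would seldom be missed. The interval around a tie would still reach about 1.29, so the conclusion softens but survives.

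On synergy, the lack of power is openly disclosed where the test is specified. What remains is that item 3 does not carry the same caution.

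**Conclusion.** The point holds as a mismatch between a promised conclusion and the stated hypothesis, sample size and test. The trial can show that reminders every 3 months are worse than monthly ones. It cannot establish that they are as effective. How far short it falls depends on the CV: the interval around a tie is about 0.63 to 1.59 at the plan's 0.54 and about 0.77 to 1.29 at an assumed 0.30. A true ratio of 1.5 would be non-significant about 58% of the time at the plan's CV. These figures assume that between-facility variation drives the standard error, that there is no gain from stratification, and a t reference on 19 df.

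Two stronger readings are not supported. The article does not plan to read non-significance as equivalence; that is a risk created by the wording. Nor is the superiority design at fault for lacking a margin: research question 1 does not need one, and this trial would have under 50% power at CV 0.54 for every margin tried.

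**What to change.** In Expected outcomes:

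1. Reword item 1 to: *whether monthly reminders are more effective than reminders every 3 months in sustaining the behaviour of health care aides*.
2. Add: *A non-significant difference will not be taken as evidence of equal effectiveness; the rate ratio will be interpreted with its 95% confidence interval.*
3. Bring item 3 into line with the analysis section by calling the synergy test exploratory.

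The superiority test, the model and the number of facilities stay unchanged, and no equivalence or non-inferiority margin is needed. The cost is a few sentences and a more modest claim about the cheaper schedule. The Trial status section reports 2 of 24 facilities recruited, so the wording can be settled well before any results.
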